**During 24 hours after T0**

- Obtain written (signed, dated) informed consent at the time the patient has regained consciousness and is able to provide informed consent
- Obtain the pre-mRS and BI (**retrospective**) and Home care before admission in a survey with the patient or a proxy – **see Screening**
- Patients with NCSE: transfer the EEG data to the cloud (according to the working instructions)

**From initiation of intervention (T0) until the end of the study**

- Assess for adverse events (chapter 7)

**Visit 2 (V2)****Day of discharge/day before discharge from hospital or day 30 (+/- 1 day), whatever is sooner**

- Record the following data (eCRF)
  - day of recurrence of seizures or convulsive SE after successful intervention/ day of detection of NCSE (EEG) after successful intervention
  - day of first EEG-detection of terminated NCSE after failed intervention
  - further antiepileptic treatment after intervention: medication, dosage, type and frequency of application including stop of medications
  - reason for withdrawal of treatment with VPA or LEV
  - acute renal failure with or without dialysis
  - acute pancreatitis
  - acute hepatic failure
  - lab analysis: level of ammoniaemia and subsequent repetitions, as ordered by treating physician \*
  - type of infections requiring i.v. antibiotic treatment
  - start and stop of invasive/noninvasive ventilation (day)
  - development of delirium and treatment
  - complications requiring surgery or invasive diagnostics/ therapy
  - etiology of SE (cerebral focus, metabolic/infectious/toxic conditions, noncompliance/withdrawal/change of antiepileptic medication)
  - home care after hospital stay (if applicable)
- Administer GCS and perform brief neurological exam: orientation, horizontal extraocular movements, motor drift of both arms and legs, sensation, language.
- Obtain mRS and BI

\* **NOTE:** As soon as an otherwise unexplained disturbance of consciousness, nausea or hypotension occurs in duration of treatment with VPA during the hospital stay the efforts of clarification **must** include the detection of a potential hyperammonemia.

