### **3.2.2 Essential technical equipment at the trial sites and involvement of other facilities in the trial**

The following equipment is required:

- ⇒ Trained personnel for sampling, preparation and shipment of blood specimen for analysis at local laboratory (including determination of the drug levels VPA and LEV).
- ⇒ Refrigerators for short-term storage of lab specimen,
- ⇒ PC for electronic data entry (electronic CRF),
- ⇒ PC and internet access to transfer the EEG data,
- ⇒ Facilities to conduct an EEG for the duration of one hour.

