#### During 60 minutes after initiation of intervention

- Monitoring of blood pressure as clinically indicated, heart rate and oxygen saturation continuously during 60 minutes after initiation of infusion. Only parameters requiring emergency treatment (as hypotension, tachyarrhythmia, low oxygen saturation) have to be recorded.
- **In case of NCSE:** It is not possible to replace the EEG device AFTER the start of intervention. The EEG has to be recorded until 60 minutes after the start of intervention

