#### Randomisation procedure

Randomisation lists are created by statistical software. Blocks of randomly chosen length are created as realisations of random samples and stringed together to a list.

ZKS Leipzig delivers one randomisation list per centre each to the central pharmacy Erlangen. Beginning with the first entry in the randomisation list, the staff of the pharmacy packs medication kits for one patient each. Every kit is labelled by a consecutive ID number and contains a sealed opaque envelope revealing the information about the medication. A pre-defined number of kits are packed into a package and are sent to the trial sites. The medical personal in the trial sites is obliged to take the set with the lowest ID number. Treatment failure is defined as clinical evidence of epileptic activity and / or persistent electroencephalographical ictal activity consistent with NCSE according to the Salzburg criteria 15 minutes after the initiation of intervention or recurrence of ictal activity (in case of NCSE return of EEG patterns to baseline status after initial treatment response) during the further 45 minutes observing period which leads to immediate unblinding of medication. In case of treatment success, drug therapy will be unblinded after 60 minutes to ensure appropriate further treatment (see Figure 1). The investigator is responsible that the envelope is not opened before.

Every trial site is equipped first with a start package of fixed number of medication sets. The size of further packages may be adapted in accordance to the accrual of the trial sites.

The trial sites inform the ZKS about every included patient and transfer the medication ID. Matching the randomisation list with the correspondent list from the central pharmacy Erlangen, the ZKS is able to oversee the randomisation process and the medication logistics.

By study design most of the effects in secondary endpoints cannot be unequivocally attributed to the trial medication. Regarding the parameters, they are not susceptible to biased evaluation either. To minimize bias arising from evaluation of EEG-patterns, EEG evaluation trainings shall be performed. Each trial site will be equipped with working instructions to ensure homogeneity of procedures. These working instructions will cover:

1. The preparation of the intervention
2. The procedures during 60 minutes after the start of intervention
3. The procedure of uploading the EEG data
4. The report of AEs.

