#### Blinding

Patients as well as treating physicians are blinded until 60 min after initiation of the infusion at the latest. After 60 minutes at the latest, the medication is unblinded in order to be able to decide on further treatment.

For unbiased evaluation of the primary endpoint final EEG is assessed by two expert raters (EEG reference board) blinded to treatment arm allocation.

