#### Efficacy

- Time from initiation of trial intervention to cessation of eSE within 60 minutes
- Neurological status (including vigilance) 60 minutes after initiation of intervention

- Difference of blood levels of VPA and LEV before and 60 minutes after initiation of intervention
- Recurrence of seizures or nonconvulsive/ convulsive SE after initially successful intervention
- For patients who failed the primary endpoint, number of patients in whom SE ceased during 60 minutes after initiation of intervention according to the treating physician
- For NCSE patients who failed the primary endpoint, time to first cessation, as verified by EEG
- Number of patients with SE-associated ventilation until hospital discharge
- Functional outcome at discharge, defined by Barthel Index (BI) and modified Rankin Scale (mRS)

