### 8.5.2 Planned Methods for Analysis

The primary endpoint will be analysed by means of a generalized mixed linear model with binomial link function incorporating randomisation arm as fixed and centers as random effects. Odds ratios are calculated as effect sizes incl. 95% confidence interval (CI) and tested. In secondary analysis, the cessation rates are tested by  $\chi^2$  test. Cessation rates and their difference with 95% CI following Wilson (Newcombe 1998b, 1998a) are calculated.

Other event rates are estimated with 95% CI (Wilson) and possibly are compared by chi-squared test without continuity correction and by mid-p test if expected numbers are too small, respectively. Time-to-cessation is analysed by time-to-event methods (Kaplan-Meier estimates and logrank test).

Latency between start of SE and 1) application of the last benzodiazepines before the start of study medication and 2) start of study medication is analysed by descriptive statistics for CSE and NCSE separately. An adjustment of the primary analysis for these covariates will be considered.

(Generalized) mixed linear models are built for the other endpoints (e.g. questionnaire scores) as well for longitudinal analyses similar to the primary endpoint.

In secondary analysis, the inclusion of the Status Epilepticus Severity Score (STESS, Rosetti et al. 2008) into multiple models for several endpoints is envisaged.

Explorative subgroup analyses are performed for female / male patients, generalized or focal CSE with impaired consciousness/ focal CSE without impaired consciousness / NCSE with coma / NCSE without coma. Although the trial is not powered for these comparisons, the analyses will give valuable new insights on the subtypes of SE and elderly patients.

Due to the short period the patient is in the study, we expect that missing data will be a minor problem. Multiple imputation is envisaged only if a high proportion of questionnaire data is missing. The definition and calculation of derived variables as well as a detailed description of the analysis method is stipulated in the statistical analysis plan. It will be established when data from 10% of the patients are input into the database. This proportion is absolutely necessary to take main properties and relationships of the data into consideration.

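### Time to EEG-verified cessation in NCSE failures is collected only as the calendar day of detection, a coarse upper bound that mixes cessation with the timing of unblinded, unscheduled EEGs

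*Protocol*

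**What the plan says.** The English synopsis (among the key secondary endpoints), section 2.2 and section 8.2.2 all list this efficacy endpoint: "For NCSE patients who failed the primary endpoint, time to first cessation, as verified by EEG". The German synopsis words it as the time to the first EEG-supported proof that the NCSE has ended after a failed intervention.

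The matching data item is in the Visit 2 list of section 6.3, completed at discharge or day 30, whichever is sooner: "day of first EEG-detection of terminated NCSE after failed intervention". No other data item for this endpoint is named.

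On EEG, section 6.3 says "The EEG has to be recorded until 60 minutes after the start of intervention", and section 3.2.2 asks sites for "Facilities to conduct an EEG for the duration of one hour". Visit 2 includes no EEG. The recording up to 60 minutes goes to the blinded EEG reference board (sections 8.1.1 and 11).

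On blinding, section 8.1.1 says that recurrence "during the further 45 minutes observing period which leads to immediate unblinding of medication", and for everyone: "After 60 minutes at the latest, the medication is unblinded in order to be able to decide on further treatment". Section 6.5 leaves treatment after the infusion to the responsible clinicians.

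On analysis, section 8.5.2 says "Time-to-cessation is analysed by time-to-event methods (Kaplan-Meier estimates and logrank test"). Section 8.4 calls the secondary analysis mainly explorative and gives no power for it.

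**The concern.** The endpoint is a time, but the form collects a day, and the day belongs to an EEG that nobody was required to do. Cessation at minute 25 and cessation at 12 hours can carry the same or adjacent days. Cessation shortly after an EEG that still shows NCSE is dated to the next EEG, whenever that comes. The date of the last EEG still showing NCSE is not collected, so the interval that contains the true time cannot be rebuilt.

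EEGs after 60 minutes are ordered with the allocation known. If monitoring is closer after one drug than after the other, detection comes earlier in that arm even when the status stops at the same time in both. Section 8.1.1 states that the secondary parameters are not open to biased evaluation. For this endpoint that is too confident: the timing of assessment is open-label even if the reading of each EEG is sound.

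An analysis plan can choose a method for interval-censored data, but it cannot recover clock times or a last ictal EEG that were never entered.

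**Working it through.** **1. Endpoint against data item.** Three cases show what the day field keeps.

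- Failure at 15 minutes, cessation at minute 25: visible to the minute on the trial's own EEG; the Visit 2 item keeps only a day.
- Early response, then recurrence before 60 minutes: the first cessation precedes the failure, whereas the Visit 2 item asks for detection after a failed intervention. The two can refer to different events.
- Cessation after 60 minutes: known only to lie between the last EEG with NCSE and the first without. The form keeps the day of the second and nothing of the first.

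**2. The plan's own figure.** The protocol gives no number for this endpoint. Its sample size concerns the primary endpoint (60% v 47%, two-sided 5%, 80% power) and reproduces: n per arm = (1.96 + 0.8416)² × (0.60×0.40 + 0.47×0.53) / 0.13² = 7.849 × 0.4891 / 0.0169 = 227.15, or 454 in total. Nothing here touches it.

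**3. Patients concerned.** Planned failures are 227 × 0.40 = 90.8 on VPA and 227 × 0.53 = 120.3 on LEV. The NCSE share is not given. Assuming 30% gives 27 + 36 = 63 patients; assuming 50% gives 45 + 60 = 105.

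**4. Detection lag.** If EEGs come every g hours from a random starting point, the mean lag from cessation to detection is g/2: 12 h, 18 h and 24 h for g = 24, 36 and 48. An arm difference of 24 v 36 h therefore shifts detection by 18 − 12 = 6 h with no drug effect.

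**5. What that shift does to a logrank test on days.** Assumptions, none from the protocol: exponential cessation times with the same median in both arms, EEGs every 24 h in one arm and every 36 h in the other, random clock time at the start, detection rounded to calendar day, everyone followed to cessation, and 63 or 105 patients. Share of simulated trials with p < 0.05 (batches of 400 to 1,000):

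| Assumed median | False positives |
|---|---|
| 6 h | 31–53% |
| 12 h | 20–31% |
| 24 h | 11–15% |
| 48 h | 8–10% (5% and 8% in a 1,000-run repeat) |

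Each range covers both sample sizes and the repeat runs. At 48 h the 400-run Monte Carlo standard error is √(0.09×0.91/400) = 1.4 points, so the excess over 5% is barely detectable. With equal 24 h intervals the rate was 4–6%, so unequal EEG timing causes the excess. At a 6 h median, 24 v 30 h gave 12–18% and 24 v 48 h gave 81–97%.

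**6. Loss of resolution without any bias.** With assumed true medians of 3 h v 6 h and daily EEGs in both arms, the logrank test detects the difference in 75–94% of trials on exact times but in only 21–37% on detection day.

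**The case against.** The strongest reply is that the endpoint is a detection time by its own wording. The German synopsis says so outright, and the English text says verified by EEG. On that reading the Visit 2 item captures the right event. This stands, and it narrows the criticism to two things: the day is coarse, and its timing depends on unscheduled EEGs ordered without blinding.

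A reader might infer that the endpoint records only when clinicians ordered EEGs and says nothing about when the status stopped. The documents do not support that. The detection day bounds the cessation time from above, and the board-read recording covers the first hour, so cessations in that hour are recoverable. An exception may be patients enrolled with clinically defined NCSE because no EEG was available (section 4.1).

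A reader might also infer that the protocol commits this endpoint to a naive logrank test. The sentence in section 8.5.2 more naturally refers to time to cessation within 60 minutes. It does not name the NCSE-failure endpoint, and detailed methods are left to the analysis plan. Only the data capture is fixed here.

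Finally, false-positive rate and power are weak benchmarks. The endpoint is exploratory and restricted to treatment failures, a group formed after randomisation (planned 40% v 53%) who then receive clinician-chosen treatment. Even exact times would not give a randomised comparison of the drugs. This also stands, and it lowers the importance of the point.

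**Conclusion.** The point holds as a data-capture weakness. The recorded day is a coarse upper bound on cessation, it mixes cessation time with EEG timing, and the information needed to separate them is not collected. The loss of hour-level information is certain. An arm difference in EEG frequency is only a possibility: nothing in the protocol shows that one will occur.

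If it does occur, its effect depends on inputs the protocol does not give. At 24 v 36 h it ranges from near nominal (8–10% or less) at a 48 h median to 31–53% at 6 h. These figures show direction and sensitivity and are not a forecast. The primary endpoint and N = 454 are unaffected. This is a change to consider, not a condition for the trial.

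**What to change.** - **First hour:** have the EEG reference board note the minute of any cessation in the T0–T60 recording it already reads.
- **Visit 2:** replace the day by two date-time entries: the last EEG still showing NCSE and the first EEG showing cessation.
- **Analysis and reporting:** treat the time as interval-censored between those two points. Report it as descriptive time to EEG confirmation, with a note that EEG timing after 60 minutes is unblinded and possibly informative.

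The cost is slightly more data entry, one extra item in the board's reading and a different method for one endpoint. No extra EEG or reader is needed, and clinical care does not change.

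The gain is partial. In the 3 h v 6 h example, a correctly specified parametric interval-censored test on daily EEGs reached 49–72% power, better than detection days but below the 74–93% on exact times in the same runs. Interval censoring held the error near 5% only because EEG times were simulated as independent of cessation. If clinicians order EEGs in response to clinical change, some bias remains.

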## 8.2 End Points

### 8.2.1 Primary End Point

Primary endpoint is the effectiveness of intravenous valproate (VPA) or levetiracetam (LEV) to terminate eSE and maintain control of epileptic activity **up to 60 minutes** after initiation of the trial intervention defined:

- ⇒ for patients with CSE: cessation of convulsions within 15 min after initiation of infusion, subsequent stable cessation of convulsions during 60 minutes after initiation of infusion.
- ⇒ for patients with NCSE: cessation of EEG signs of NCSE according to Salzburg criteria (Leitinger et al. 2016) within 15 min after initiation of infusion, subsequent stable cessation of ictal EEG activity according to the Salzburg criteria during 60 minutes after initiation of infusion as evaluated by the external EEG reference board.

Evaluation of this endpoint is possible for each patient.

Statistically, the time to cessation as well as the success rate is evaluated.

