## **11 REFERENCE EVALUATIONS**

All study related electroencephographical data will be evaluated by a central committee consisting of two external expert reviewers (EEG reference board) who are medical specialists in neurology and also experts for epileptology. They are blinded to the treatment; clinical data of the patient will not be provided. For the purpose of the external review every trial site transfers the pseudonymized EEG data to a study specific cloud, the related server is located at the ZKS Leipzig. Access to the EEG data is restricted to the reviewers. Each trial site is only permitted to upload data. The pseudonymisation can be realized in the following manner:

- ⇒ the clinical recording of a patient will be stopped and a new record labelled with the patient ID, will be started
- ⇒ after converting the data in an edf file the heading with the patient related information can be read out in a text editor and pseudonymisation can be checked before the transfer to the cloud

Reference evaluation of the EEGs will be completed within 1 month. Disagreement between the two expert raters will be resolved by discussion. If the EEG reference board disagrees with the diagnosis NCSE in more than 25% of all cases contributed by a given trial site over a year the trial staff of that site will undergo additional training.

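### Visit 2 asks for the day NCSE ended only after a failed intervention, in practice as the site judges it, while the endpoint using that day is defined by the EEG board's verdict

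*Protocol*

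**What the plan says.** **Collection.** Protocol section 6.3, Visit 2, contains two items that depend on how the intervention turned out. The first is the "day of recurrence of seizures or convulsive SE after successful intervention", with its EEG counterpart, the "day of detection of NCSE (EEG) after successful intervention". The second is the "day of first EEG-detection of terminated NCSE after failed intervention". The visit takes place on "Day of discharge/day before discharge from hospital or day 30 (+/- 1 day), whatever is sooner".

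**Analysis.** Section 8.2.2 lists the efficacy endpoint "For NCSE patients who failed the primary endpoint, time to first cessation, as verified by EEG", which the synopsis counts among the key secondary endpoints. Section 8.2.1 defines the primary endpoint for NCSE as EEG cessation within 15 minutes and stable control "during 60 minutes after initiation of infusion as evaluated by the external EEG reference board". Section 8.2.2 also lists recurrence after initial success, without saying who decides that the intervention succeeded.

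**Flow of information.** Section 11 says: "Reference evaluation of the EEGs will be completed within 1 month". It restricts access to the EEG data to the two reviewers and adds: "Each trial site is only permitted to upload data".

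**Recurrence elsewhere.** Section 7.1.3 lists recurrence for recording in the CRF, again only following success. The Schedule of Assessments and Procedures has a row for recurrent seizures or SE that runs to discharge with no such condition.

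**The concern.** A field that is asked only under a condition is filled in according to whoever judges that condition when the form is completed. Here the site completes the form, but the board defines the analysis group. Where the two differ, a patient can belong to an endpoint in the analysis without having been asked for the value that the endpoint needs.

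The disagreements are unlikely to be a random sample. They will tend to lie among patients whose EEG is hard to read, and the missing dates belong to patients whose NCSE, on the board's reading, outlasted the first hour. Time to cessation among failures would then lean on the patients who stopped early.

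**Working it through.** The plan gives no figure on this point to reproduce. The primary comparison and its 454 evaluable patients do not depend on it. The check sets the sections side by side.

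**1. Who decides at the bedside?** Under section 6.3 the site checks for cessation at T15 and for recurrence until T60. Section 8.1.1 ties unblinding to that judgement. The site therefore holds its own verdict within the hour.

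**2. Who decides in the analysis?** For NCSE the primary endpoint is the board's reading (section 8.2.1). An endpoint restricted to patients who failed the primary endpoint inherits that classification.

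**3. Can the site use the board's verdict at Visit 2?** EEG data go to the cloud within 24 hours of T0 (section 6.3). A month from then ends at about day 30, and Visit 2 is at discharge or day 30, whichever comes first. For a patient discharged earlier, the reading can arrive after the form is due. No section describes returning an individual verdict. That the site branches on its own view is an inference from timing and access. It is the only workable reading, but it is not stated.

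**4. Does the protocol expect disagreement?** Yes. Section 8.2.2 counts primary-endpoint failures in whom the treating physician judged that SE had ceased within the hour.

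**5. What is lost in each case (NCSE patients)?**

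| Site | Board | Termination day | Recurrence |
|---|---|---|---|
| success | success | not needed | asked |
| failure | failure | asked | not needed |
| success | failure, cessation visible by T60 | can be read from the uploaded EEG | not needed if the board's class applies |
| success | failure, no cessation by T60 | needed, **not asked** | not needed if the board's class applies |
| failure | success | not needed | schedule: recorded; sections 6.3 and 7.1.3: not called for |

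The fourth row is the clear gap. The trial EEG need only run to 60 minutes, and no later trial EEG is scheduled. The Visit 2 item is thus the only planned source, and it does not apply as worded. Every time in this row exceeds 60 minutes. If these patients drop out, the estimated time to cessation is biased toward shorter values.

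The last row is a conflict between sections. It is not a demonstrated loss.

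**6. Size.** The documents give neither the NCSE share nor the rate of site-board disagreement on outcome. As an assumption, take 30–70% NCSE among the 477 to be randomised and 5–20% disagreement:

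- low: 0.30 × 0.05 × 477 = 7.2 patients (1.5%)
- high: 0.70 × 0.20 × 477 = 66.8 patients (14%)

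This counts disagreement in both directions. The fourth row is only a part of it, and nothing in the protocol says how large a part.

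**The case against.** A reader might infer that data are missing for every patient on whom site and board disagree. The documents do not support that. The NCSE EEG is recorded to 60 minutes and uploaded whatever the site thought, so a board failure who stopped between 15 and 60 minutes, or stopped and relapsed, can be dated from it. Recurrence has its unconditional schedule row, and adverse events are recorded from T0 to the end of the study. These objections stand, and they confine the clear gap to one cell of the table.

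A reader might also infer that the recurrence rate is biased downward because unasked patients count as free of recurrence. No section says that they would. Section 8.2.2 does not name the board as classifier for this endpoint, and if the site's view applies, collection and analysis agree. What remains is an inconsistency to resolve.

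The 25% in section 11 is tempting as a disagreement rate. It is a yearly per-site retraining threshold for disagreement on the NCSE *diagnosis*. It says nothing about agreement on outcome and is not used here.

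Two practical arguments remain. Section 10.3 allows manual queries after data entry, so a late board verdict could still prompt the site to look up the date. That is possible, but no section plans it. Section 8.4 also calls the analysis of secondary endpoints mainly explorative. That limits the weight of the point but does not make the item fit its endpoint.

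**Conclusion.** The mismatch is real but narrow. For NCSE patients whom the site rates a success and the board a failure, and whose uploaded EEG shows no cessation by T60, the plan has no source for the termination day that a key secondary endpoint requires. The loss is informative because these are the longest times. Separately, sections 6.3 and 7.1.3 conflict with the schedule on whether recurrence is recorded for all patients, and the classifier for initial success is not named.

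The primary endpoint, the analysis set and the sample size are untouched. The conclusion rests on two assumptions: that the site answers the conditional items from its own judgement, and that board verdicts do not routinely reach it before Visit 2. The number affected cannot be derived from the documents. The 7 to 67 discordant patients rest on assumed rates and overstate those with lost data. The change is worth making because it is cheap now, and an analysis plan cannot recover a date that was never requested.

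**What to change.** - In section 6.3 and the eCRF, drop the success and failure conditions. For **every** patient, record any seizure or SE after T60 with its date. For **every NCSE** patient, record the date of the first routine EEG after T60 that shows no NCSE, or that no such EEG was done.
- Keep the words after T60 in the second item. Without them, a site that believed NCSE had ended at T15 would enter the same early EEG that the board rejected.
- Align sections 6.3 and 7.1.3 with the unconditional row in the schedule of assessments.
- In section 8.2.2, state that the board's verdict assigns NCSE patients to the success and failure endpoints in the analysis, including recurrence.

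The cost is two reworded eCRF items, matching text edits and slightly more data entry. No new examination is needed. Patients with no later EEG will still lack a date, but the entry that none was done separates them from an item left blank.
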